### Interim analyses

To enhance monitoring of safety in the supra-marginal resection group, we plan to submit safety reports every 6 months to the DSMB including 30-day mortality data and all serious adverse events (both expected and unexpected) for their review. The DSMB will have formal annual meetings unless they decide to have them earlier based on the submitted safety reports. The initial DSMB meeting will occur either following accrual of the first 10 participants or 6 months after initiation of the study, whichever comes first.

This study will be stopped prior to its completion if (1) the intervention is associated with adverse events that call into question the safety of the intervention, (2) difficulty in study recruitment or retention will significantly impact the ability to evaluate the study endpoints, (3) any new information becomes available during the trial that necessitates stopping the trial, or (4) other situations occur that might warrant stopping the trial.

### Methods in analysis to handle protocol non-adherence and any statistical methods to handle missing data

All randomized patients will be included in the final analysis according to the ITT principle. Patients who are randomized but who were subsequently determined not to meet the eligibility criteria will not be included in the primary analysis but will be followed to assess safety endpoints.

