## Methods: participants, interventions, and outcomes

### Eligibility criteria

The following are the inclusion criteria:i)Radiographic evidence of a GAD-enhancing brain tumor consistent with HGG.ii)Age ≥ 18 to < 80 years.iii)Karnofsky Performance Score ≥ 60.iv)The tumor is in an anatomical location that is considered safe for surgical resection (Additional file 1).

The following are the exclusion criteria:i)Multi-focal tumor, gliomatosis cerebri (≥ 3 lobes of the brain affected), and tumors crossing the midline or with leptomeningeal enhancementii)Previous craniotomy for tumor excision (stereotactic biopsy is permitted)iii)Intraoperative histopathological diagnosis not consistent with HGGiv)Known metastatic cancerv)Uncorrectable coagulopathyvi)Unable to obtain GAD-enhanced brain MRI

The selection of surgeons for this trial will be based on the criteria to demonstrate an adequate level of surgical expertise for the resection of HGGs (Additional file 2). Figure 1 illustrates a guide for safe anatomical tumor locations amenable to standard GTR and supra-marginal resection.

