#### Criteria for discontinuing or modifying allocated interventions

At their own discretion, participants may withdraw from the study at any time and for any reason. Study participants may also be withdrawn from the study at the discretion of an investigator for reasons such as, but not limited to safety, participant compliance or behavioral concerns. All participants need to have a confirmed final pathological diagnosis of high-grade glial tumor (i.e., grade 3 or higher) to be included in the primary intention-to-treat (ITT) analysis. Participants with any other final diagnosis will not remain in the study, but data will be collected to provide additional safety information.

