***Received > 90% of planned dose***			
***Early discontinuation < 50%***			
***Disease progression***			
***Toxicity***			
***Others***			

### Safety criteria

During this pilot study, several safety precautions are being implemented:i)A clearly defined definition of “surgically safe” anatomical criteria.ii)Confirming anatomical suitability by a second designated neurosurgeon centrally.iii)A central adjudication committee, comprising two qualified neurosurgeons, will confirm the suitability of all enrolled cases on an annual basis.iv)Establishing appropriate surgical expertise and volumes for participating surgeons (Additional file 2),v)Mandating minimum intraoperative use of 3D neuronavigation and neurophysiologic monitoring to guide resections for all patients.vi)Incorporating multiple interim safety analyses by the Data and Safety Monitoring Board (DSMB).

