### Assignment of interventions: allocation

#### Sequence generation

Eligible patients will be approached for enrollment either in the preoperative clinic or after hospital admission. Surgery will take place within 14 days of enrollment. Randomization will be done within 3 days prior to the scheduled surgery and will occur in a 1:1 ratio.

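### The protocol promises an all-randomised ITT analysis but removes patients from the primary 'ITT' set for final pathology or any later-determined ineligibility, with no safeguard on how that is decided

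*Protocol article*

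**What the plan says.** Three rules in the protocol article define who is analysed.

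- In the section on non-adherence and missing data: "All randomized patients will be included in the final analysis according to the ITT principle".
- In the next sentence of that section: "Patients who are randomized but who were subsequently determined not to meet the eligibility criteria will not be included in the primary analysis". The sentence goes on to keep these patients under follow-up for safety endpoints.
- Under Criteria for discontinuing or modifying allocated interventions, patients need a "confirmed final pathological diagnosis of high-grade glial tumor (i.e., grade 3 or higher) to be included in the primary intention-to-treat (ITT) analysis". Patients with another final diagnosis leave the study, though data are still gathered on them for safety.

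On timing, the Eligibility criteria admit patients on "Radiographic evidence of a GAD-enhancing brain tumor consistent with HGG", and Sequence generation says "Randomization will be done within 3 days prior to the scheduled surgery". Exclusion criterion iii concerns histology obtained during the operation. A previous biopsy does not bar entry ("stereotactic biopsy is permitted"), so histology may be known earlier in some patients.

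On knowledge of the arm, Who will be blinded states that surgeons cannot be blinded. Concealment mechanism accepts that at some sites the research team will also know the allocation.

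**The concern.** The first two rules conflict, and the third attaches the ITT label to a set that is not ITT. This is not a detail left to an analysis plan, because the article states each rule itself.

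The exclusions also act after randomisation. One ground, final pathology, is a trait the tumour had before allocation. The other is open-ended: it covers every eligibility criterion, including whether the location was anatomically safe, and sets no limit on when, by whom or on what information ineligibility is determined. If such decisions can be made by people who know the arm or the outcome, the two groups compared are no longer certain to be those that randomisation formed.

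At stake are overall survival, progression-free survival and the adherence proportions. Under Adherence to protocol, the pilot data are also to be used to estimate the phase III sample size and, if the protocol does not change materially, to be included in that trial. A defect in the pilot's analysis set could then pass into the definitive comparison.

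**Working it through.** **1. Can the rules be reconciled as written?** One could read the 'final' analysis as all randomised patients and the 'primary' analysis as a subset. That reading fails for efficacy. The section on discontinuing interventions calls the restricted set the primary ITT analysis and takes the other patients out of the study except for safety data. Overall survival is listed under preliminary efficacy in Secondary outcomes, not under safety, where only 30-day mortality appears. An all-randomised survival set is therefore not assured.

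**2. The plan's own figures.** They reproduce, and none allows for exclusions after randomisation.

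- Recruitment target: 6 centres × 24 months ÷ 2 = 72, equal to the sample size (36 per group).
- Exact Poisson 95% interval for a count of 72: 56.3 to 90.7, against the stated 56 to 91.
- Phase III deaths (Schoenfeld, hazard ratio 0.7, 80% power, two-sided 5%): 4 × (1.960 + 0.842)² ÷ (ln 0.7)² = 246.8, rounded up to 247, as stated.

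**3. Size of the analysis set.** The exclusion share *e* is an assumption. Remaining = 72 × (1 − *e*). Number to randomise = target ÷ (1 − *e*), rounded up.

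| Assumed *e* | Remaining of 72 | Randomise to analyse 72 | Randomise to analyse 295 |
|---|---|---|---|
| 2% | 71 | 74 | 302 |
| 5% | 68 | 76 | 311 |
| 10% | 65 | 80 | 328 |
| 15% | 61 | 85 | 348 |

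**4. Adherence criterion.** Adherence to protocol requires overall survival to be measured in at least 90% of enrolled patients. If survival were not collected on excluded patients, 7 exclusions would leave 65/72 = 90.3% and 8 would leave 64/72 = 88.9%, below the line.

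**5. How far selective exclusion could move survival.** This is a worst case, not a forecast. Assume no true effect, 36 per arm, exponential survival with the stated 14-month median and censoring at 24 months. Remove the *m* earliest deaths from one arm only. The hazard ratio is the geometric mean over 20,000 simulated trials.

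For 12-month mortality, 1 − exp(−ln 2 × 12/14) = 44.8%, or 16.13 expected deaths of 36. After removal it is (16.13 − *m*) ÷ (36 − *m*).

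| *m* removed | Mean estimated hazard ratio | 12-month mortality in that arm |
|---|---|---|
| 0 | 1.00 | 44.8% |
| 1 | 0.96 | 43.2% |
| 2 | 0.92 | 41.5% |
| 3 | 0.89 | 39.8% |
| 4 | 0.85 | 37.9% |

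Exclusion unrelated to arm and outcome would not produce this shift.

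**The case against.** **What stands in the plan's favour.** Safety follow-up is retained, and the safety outcomes include NIHSS, mRS, EQ-5D and 30-day mortality. A patient with a new deficit who is later judged ineligible is not lost to the safety assessment. Tumour type precedes randomisation, so exclusion on pathology read blind to arm carries little bias. The pilot is declared not powered for superiority, its primary outcome is a descriptive rate, and progression rests on recruitment and on the DSMB's concerns. Pooling into phase III is conditional.

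**Stronger readings that the documents do not support.**

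- A reader might infer that the annual committee, which "will confirm the suitability of all enrolled cases on an annual basis", will remove supra-marginal patients with poor outcomes. Nothing links its findings to removal from analysis or says that it sees outcomes. Safety criteria also provides a separate central check of anatomy by a second neurosurgeon.
- A reader might infer that the supra-marginal arm yields more tissue and so a different diagnosis. Both arms plan to resect at least 95% of the enhancing tumour, and the article does not suggest that the extra margin changes the grade.
- A reader might infer that a single exclusion turns a met target of 72 into a missed one. The primary feasibility outcome, its analysis and the progression rule count patients enrolled, allocated, randomised or recruited. None makes the count depend on final pathology.
- A reader might infer that non-glioma patients disappear from phase III planning. Data on them are still collected, so their number remains available.

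These points narrow the concern. They do not reconcile the conflicting rules or put a limit on later-determined ineligibility.

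**Conclusion.** The contradiction is in the text and does not depend on any figure. The primary analysis set is called ITT but is restricted after randomisation, and one ground for restriction has no stated blinding, timing or pre-randomisation limit. Exclusion that depends on arm or outcome is a possibility left open, not something the documents show or predict. Its direction is not established either.

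The exposure is confined to overall survival, progression-free survival, adherence, the event rate carried into phase III planning, and any pooled pilot data. Its size cannot be stated, because the documents give no exclusion rate. The shares of 2% to 15% and the removal of one to four early deaths are assumptions that show scale only.

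**What to change.** Reconcile three places: Eligibility criteria (exclusion iii), Criteria for discontinuing or modifying allocated interventions, and the section on non-adherence and missing data.

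1. Define ITT as all randomised patients, analysed as allocated. Use it for recruitment, adherence, safety, overall survival and progression-free survival, and keep collecting survival on every randomised patient.
2. Name the confirmed high-grade glioma set modified ITT. Have pathology assign the diagnosis without knowledge of arm, and report this result beside the ITT result.
3. Do not exclude patients for any other ineligibility judged later. Report it as a protocol deviation.
4. Report the number of non-glioma and ineligible patients, with reasons, by arm.
5. State that the recruitment target counts all randomised patients.

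Exclusion iii may also govern what happens once intraoperative histology is known. That is a clinical matter. Here it needs only to be made consistent with the analysis rules.

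The cost is wording and continued survival follow-up of a few patients. The downside is that a few patients without high-grade glioma slightly dilute the all-randomised survival description, which the modified-ITT result alongside makes visible.

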### Plans to give access to the full protocol, participant-level data, and statistical code

The authors are open to de-identified data including granting public access to the full protocol, participant-level dataset, and statistical code as long as requesting investigators have an IRB-approved protocol.

### Adverse event reporting and harms

Adverse event information will be entered into the CRF in a timely manner and no later than 15 days from the time the investigator becomes aware of the event. Information about any unexpected serious adverse events that are attributed to the study intervention will be entered into the CRF in a timely manner/within 72 h from the time the investigator becomes aware of the event.

### Frequency and plans for auditing trial

Site monitoring will be conducted to ensure the safety of human study participants and the protection of their rights and well-being. Monitoring will verify that collected study data is accurate, complete, and verifiable by source documentation and that the study is conducted in accordance with the protocol and operating procedures. The delegated monitor will evaluate the study processes and documentation based on the approved protocol/amendment(s), the International Council for Harmonisation of Technical Requirements for Pharmaceuticals for Human Use (ICH), E6: Good Clinical Practice guidelines (GCP), and institutional policies.

### Dissemination plans

Plans to communicate the trial results to participants, health care professionals, and the public will be via publications which will adhere to the Uniform Requirements for Manuscripts Submitted to Biomedical Journals of the International Committee of Medical Journal Editors.

## Discussion

Recent studies demonstrate survival advantages comparing standard gross total resection of GAD-enhancing tumor to supra-marginal resection with no additional perioperative surgical risk [20]. However, the current quality of evidence is low and under-powered, limited to prospective studies and retrospective case series. There are no current practice guidelines and the philosophy of surgical resection is guided by individual surgeon preferences on an individual patient basis. This creates additional uncertainty and is potentially detrimental to our patients as supra-marginal resection could potentially increase the risk for surgery-related post-operative deficit or conversely potentially increase overall survival. This clinical equipoise demonstrates the need for an adequately powered RCT to determine whether a supra-marginal resection can have a positive impact on survival for patients with HGGs. Our pilot multi-center RCT aims to test the feasibility, including recruitment potential and safety of comparing standard gross total resection of GAD-enhancing tumor versus supra-marginal resection. The aim is to ultimately prepare for a larger, definitive multicenter RCT.

## Trial status

The trial was registered with ClinicalTrials.gov (NCT04737577) on February 4, 2021.

## Abbreviations

AE: Adverse event/adverse experience
CCTS: Centre for Clinical Trial Support
CRF: Case report form
DSMB: Data and Safety Monitoring Board
eCRF: Electronic case report form
EQ-5D: EuroQol-5D
GAD: Gadolinium
GCP: Good Clinical Practice
GTR: Gross total resection
HGG: High-grade glioma
ICF: Informed consent form
ICH: International Council for Harmonisation
IQR: Interquartile ranges
ITT: Intent-to-treat
mRANO: Modified Response Assessment in Neuro-oncology
MRI: Magnetic resonance imaging
mRS: Modified Rankin Scale
NIHSS: National Institutes of Health Stroke Scale
pCRF: Paper case report form
PHI: Personal health information
PHIPA: Personal Health Information Protection Act of 2004
PI: Principal investigator
QOL: Quality of life
RCT: Randomized controlled trial
REB: Research Ethics Board
SAE: Serious adverse event/serious adverse experience
SDM: Substitute decision-maker
SI: Site investigator
SMR: Supra-marginal resection
SRI: Sunnybrook Research Institute
STR: Subtotal resection
